#### Sequential analysis

As the recruitment in the trial until present has been slower than anticipated, we may face a scenario where we have to end recruitment before the sample size of 122 participants has been met. In this case, we plan to perform sequential analysis to assess the results of significance testing, taking sparse data and into consideration [72]. We will for the primary outcome, CANTAB-RVP, use a minimal clinically relevant difference of 0.13 and a variance of 0.0484 (corresponding to a SD of 0.22). For the secondary outcomes, we will use minimally relevant differences of 5 points and a variance of 100 (corresponding to a SD of 10 points) for both AHDH-RS assessments and a minimal clinical relevance of 0.25 points and variance of 0.25 (corresponding to a SD of 0.5 points) for both BRIEF assessments. For all outcomes, we will use a type I error of 5 %, and a type II error of 10 %. We will use the trial sequential analysis program for these analyses (http://ctu.dk/tsa/) [73–76].

### Discussion of clinical relevance

If the trial results indicate that this intervention reduces specific cognitive deficits in children with ADHD without causing any adverse reactions effects, our interpretation will be that the intervention can be an important part of a treatment plan as cognitive dysfunctions are very common in children with ADHD. Furthermore, if we find improvement in the BRIEF measures and ADHD-RS, this would suggest that the effects of the intervention could be generalized to behavior in an everyday setting.

### Monitoring of patient compliance issues

The intervention group compliance will be monitored via the computer program that records patients log on, which games they have played, and for how long.

## Discussion

This trial is a multicenter, randomized clinical superiority trial investigating the effect of a home-based 8-week intervention for children with ADHD, using a computerized cognitive training program, ACTIVATE™. ACTIVATE™ was designed to enhance a broad range of cognitive functions. The trial has several strengths: it is conducted with adequate generation of allocation sequence; adequate allocation concealment; adequate blinding wherever possible; adequate reporting of all relevant outcomes; adequate handling of incomplete outcome data; and has no for-profit bias [77–80]. The trial results will offer new and valuable contributions to the field of cognitive training in children with ADHD.

The trial also has some limitations. Due to the nature of the trial, it is not possible to blind the participants, their parents, or their teachers. A “sham” intervention for the control group was considered. However, in order to introduce an active control intervention that would function as a true placebo, we needed to be sure that this intervention had no beneficial or harmful effects, which is difficult to document. Furthermore, a placebo-training program would be somewhat boring in order to have no training effect. This would potentially cause problems with low adherence in the control group and reveal group allocation. We consequently chose a “treatment as usual” control group, thereby accepting the risk of bias regarding the blinding that this entails.

We included both drug-naïve children and children receiving pharmaceutical therapy in the trial. As the randomization procedure is stratified for this variable, it is not expected to influence the trial results. Furthermore, all children are required to be free of medication 24 hours before cognitive testing in order to influence the results as little as possible. All patients are required to perform cognitive assessments at four time points without medication. This may present a potential threat of bias in terms that patients, who are not able to function without medication for 24 hours prior to the testing, could choose not to participate in the study. In this case, some of the more severe cases with ADHD might not be represented in the study sample. Overall, inclusion of children regardless of pharmaceutical treatment status is expected to increase the external validity of the trial results.

We do not consider dropout of medical treatment during the trial a threatening issue. In Denmark, ADHD assessments, diagnostic procedures and initiation of ADHD-medications is restricted to specialists of child and adolescent psychiatry, and general practitioners are not allowed to initiate this treatment [81, 82]. This result in a lower prevalence of children and adolescents treated with ADHD-medications (prevalence in 2010 was only 1.5 % [83], compared to most other Europeans countries and certainly to most parts of the USA, and probably to a less negative public attitude toward medication. Adherence to medication in Denmark is likely higher than in many other countries. The study protocol requires medicated children to stay on medication during the intervention period. Parents are encouraged to continue the children’s medication, if they are on it at time of inclusion.

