
In all three games, the child is earning points, which are converted into coins. At the end of all three games, the child comes to a “garden” where s/he can purchase different things. The child can decide to buy things for the garden, such as plants and animals, or a car, a zoo or a house. The child can buy things after each game or can save coins to buy more expensive things later. The games are designed in a manner to be interesting and rewarding for children. All participants are doing the same kind of exercises. All participants start at the same very basic level. Progression and the level of difficulty in the games depend on the child’s performance. Hence, the level of difficulty is therefore dynamically adjusted during the trial, according to the abilities of each child or cognitive phenotype.

Training with ACTIVATE™ is home-based for 40 minutes per day, 6 days per week, for 8 weeks, resulting in a cumulative training of a maximum of 32 hours. ACTIVATE™ records each time the participant logs on and is measuring compliance, time on task and progress. All participants randomized to the intervention group are introduced to the program at the clinic. In case of any problems with the program, the participants can contact the principal investigator. C8 is also providing IT support. Parents are given verbal and written instructions that the child should use a computer with an external mouse (not an iPad or a laptop with an integrated mousepad), that training should be performed in a quiet setting, and that using headphones is mandatory. In addition, the parent are instructed to help the child remember and engage in training and to supervise the child during training sessions, to ensure adherence. We are in touch with parents, and they can contact us any time. Parents are given the instruction to supervise the child and make sure they are doing the training. There were no restrictions on the time of the day the training should be performed. However, we inform parents that most children usually like to do the exercises in the late afternoon or early evening and that parents should ensure that sessions do not conflict with school or family schedules.

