### Blinding

Due to the nature of the trial, it is not possible to blind the participants and their parents. However, we will employ blinding in all other possible areas. Investigators conducting the cognitive testing with CANTAB will be blind to the participants’ group allocation. The statistical analyses will be performed blinded with the two intervention groups coded as, for example, X and Y. The analyses will be presented blinded to the Steering Committee, who will draw two conclusions: one assuming that X is the intervention group and Y is the control group, and one assuming the opposite. After this, the blind will be broken.

To reduce the risk of biasing the rating of outcomes caused by unblinding information on group allocation, we chose an objective computerized primary outcome measure on the CANTAB. Still, the clinicians performing the CANTAB are blinded to group allocation. The treating physicians are not directly connected to the trial and do not assess or provide information on any trial outcomes. Due to regulations by the ethics committee, we were not allowed to inform the treating physician about included children to avoid that influencing the treatment in the outpatient clinic. Hence, as these clinicians were responsible for the treatment as usual (TAU) in both groups, they were also blinded to the group allocation of the child to ensure that this did not affect the TAU.

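### Teachers are declared impossible to blind without a reason that applies to them, and no step to limit their knowledge of the arm is described, although they rate two of the four secondary outcomes

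*Protocol article*

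**What the plan says.** The Blinding section says that "it is not possible to blind the participants and their parents" and continues that "we will employ blinding in all other possible areas". It does not mention teachers. It reports that the CANTAB testers, the statistical analysis and the treating physicians are all blinded.

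The limitations part of the Discussion gives a longer list: "it is not possible to blind the participants, their parents, or their teachers". The support offered is the nature of the trial and the difficulty of building a sham programme that is inert and still holds a child's interest. The same Discussion counts "adequate blinding wherever possible" among the trial's strengths.

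The Intervention group section describes the setting: "Training with ACTIVATE™ is home-based for 40 minutes per day, 6 days per week, for 8 weeks". Parents supervise the sessions and are told that "parents should ensure that sessions do not conflict with school or family schedules".

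Two of the four secondary outcomes are teacher-rated (ADHD-RS and BRIEF, teacher editions). The Multiplicity and significance section uses the secondary outcomes for further claims of benefit once the primary outcome is significant. The Discussion of clinical relevance says of improvement on BRIEF and ADHD-RS that "this would suggest that the effects of the intervention could be generalized to behavior in an everyday setting", without distinguishing parent from teacher raters.

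**The concern.** The comparator is treatment as usual with no sham, and parents know the arm. Teachers are the only raters of symptoms and behaviour for whom an attempt at blinding could be made. If they know which children are training and expect it to help, their ratings can shift in favour of the intervention without any change in the child.

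Gatekeeping and the multiplicity adjustment control chance findings across outcomes. They give no protection against a systematic shift in how an outcome is rated. What is at stake is the statement that effects carry over to everyday behaviour, which rests on these scales. The primary outcome, a computerised CANTAB measure given by blinded testers, is not at stake.

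**Working it through.** **Step 1: the texts side by side.**

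| Question | Blinding section | Discussion |
|---|---|---|
| Who cannot be blinded? | Participants and parents | Participants, parents and teachers |
| What is said of blinding in general? | To be used in all other possible areas | Adequate wherever possible |
| Reason given | Nature of the trial | Nature of the trial; no suitable sham |

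A missing sham reveals the arm to people who see, or would see, the training: the child and the parent. The teacher delivers nothing. Advice to schools is part of treatment as usual (Interventions section), but the treating specialist responsible for that care is blind to allocation. No described procedure requires the teacher to know the arm, and no described step limits the chance that the teacher learns it.

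**Step 2: the plan's own figures reproduce.** Inputs from Sample size: difference 0.13, SD 0.22, two-sided alpha 0.05, power 90%, ratio 1:1.

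n per arm = 2 × (1.960 + 1.282)² × (0.22/0.13)² = 60.2, rounded up to 61, so 122 in total, as stated.

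Inputs from Power and Table 2: effect 0.5 SD, 61 per arm. The standard error in SD units is √(2/61) = 0.181. The normal approximation gives power of 78.9% at alpha 0.05 and 60.4% at 0.0125. The two-sample t calculation gives 78.2% and 59.0%, matching the stated 78% and 59%. No figure in the plan is disputed.

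**Step 3: what a rating shift would do to one teacher-rated test.** The documents give no size for expectation bias, so a shift of b = 0.1, 0.2 or 0.3 SD is an assumption. With no true effect on the teacher scale:

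P(reject) = P(|Z + b/√(2/61)| > z), with z = 1.960 at alpha 0.05 and 2.498 at alpha 0.0125.

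| Assumed shift | ADHD-RS points (SD 10) | BRIEF points (SD 0.5) | b/0.181 | Alpha 0.05 | Alpha 0.0125 |
|---|---|---|---|---|---|
| 0.1 SD | 1 | 0.05 | 0.55 | 8.6% | 2.7% |
| 0.2 SD | 2 | 0.10 | 1.10 | 19.7% | 8.2% |
| 0.3 SD | 3 | 0.15 | 1.66 | 38.1% | 20.0% |

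The two alpha levels are the ends of the range the Power section gives for Hommel's procedure. Baseline adjustment is ignored.

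**Step 4: the gate.** The secondary outcomes are tested only if the primary has P ≤ 0.05. If the training affects no outcome at all, this happens in about 5% of trials, so false secondary claims cannot exceed about 5% whatever the rating bias. The rates in step 3 are relevant when the primary is truly improved and the gate opens. That is also when a carry-over claim would be made.

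**The case against.** The limitation is disclosed. The Discussion names teachers openly and accepts the risk of bias, and the Blinding section explains that an objective primary outcome was chosen partly for this reason. That stands and limits the weight of the point. But calling blinding impossible is not a reason for describing no attempt at it.

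A reader might infer that the plan discards blinding that was there for the taking, or that teachers are told the arm. The documents support neither. Children aged 6 to 13 who train six days a week and see their teacher at school may well talk about it. The advice about school schedules concerns timing and does not wall the teacher off. The blinding of treating physicians is not a full parallel either: the ethics committee did not allow them to be told who was included, and they supply no outcome data, whereas teachers must complete ratings. Concealment from teachers can be attempted, not guaranteed.

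A reader might also see a flat contradiction between the two sections. That is too strong: the Blinding section never says that teachers are blinded, and its list may simply be incomplete. What remains is that the reader cannot tell the intended status of the teacher ratings.

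Finally, a reader might take 38% as the trial's false-positive rate. It is not. It belongs to one ungated test, at the largest of three assumed shifts. Hommel's procedure, or the fixed sequence in Table 2 in which parent-rated ADHD-RS comes first, would lower it further.

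**Conclusion.** The point holds in a limited form. The stated impossibility is not supported by the reasons given, no step to limit teacher awareness is described, and two of the four gatekept secondary outcomes are left more exposed to expectation bias than they need be.

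The size depends on unknown rating shifts. Under the assumed range of 0.1 to 0.3 SD, with 61 per arm, no true effect on the teacher scale and an open gate, a single test is falsely positive in about 9% to 38% of trials at alpha 0.05, or about 3% to 20% at 0.0125. This is a worthwhile, inexpensive improvement to secondary evidence. It does not threaten the trial's main conclusion.

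**What to change.** For all assessments still to come (the Trial status section says recruitment is ongoing):

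- Ask families in both arms not to tell the teacher the allocation.
- Send teacher questionnaires that make no mention of the arm.
- After the ratings are complete, ask the teacher whether they knew or guessed the arm.
- Report how often teachers knew or guessed it, by arm, as description only. Awareness arises after randomisation and probably differs between arms, so label any analysis split by awareness as exploratory and non-randomised.
- Make the Blinding section and the Discussion agree: teachers are not told the allocation, but their blinding cannot be assured. If there is a specific reason why teachers must know, state it and qualify the claim of blinding wherever possible.
- In the Discussion of clinical relevance, note that parent ratings are unblinded and that teacher ratings may be.

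The cost is one instruction to families, one questionnaire item and a few sentences. Concealment will be imperfect. Children already assessed will lack both the instruction and the item, so the teacher ratings will have been collected under two conditions, which the report should say.

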## Trial status

The first participant was included and randomized in March 2013. Recruitment is currently ongoing.

## Abbreviations

ADHD: Attention Deficit Hyperactivity Disorder
ADHD-RS: Attention Deficit Hyperactivity-Rating Scale
AST: Attention switching task
BRIEF: Behavior Rating Inventory of Executive Functions
CANTAB: Cambridge Automated Neurocognitive Test Battery
CRT: Choice reaction time
DAWBA: Development and Well-being Assessment
IED: Intra-Extra Dimensional Set Shift
K-SADS: Kiddie-Schedule for Affective Disorders and Schizophrenia
MTS: Match to sample
PAL: Paired associates learning
RIAS: Reynolds Intellectual Assessment Scales
RVP: Rapid visual information processing
SWM: Spatial working memory
SOC: Stockings of Cambridge
SST: Stop Signal Task
SDQ: Strength and Difficulties Questionnaire
TAU: Treatment as usual
WFIRS-P: Weis’s scale of disability-Parent Report
